#### Physical Activity and Sleep

Daily activity and participation in PA will be measured using 2 methods: (1) the International Physical Activity Questionnaire (IPAQ) and (2) objectively, via an accelerometer (wGT3X-BT, ActiGraph LLC).

Students will complete the IPAQ at their study visit. The IPAQ was developed in 1998 and is a validated questionnaire (across 12 countries) [43] that measures the PA and exercise that individuals complete as part of their everyday lives. It characterizes PA habits in the previous 7 days and considers physical activities of daily living, recreation, sport, and leisure time. The IPAQ contains 27 questions, is self-administered, and takes approximately 10 minutes to complete.

At their study visit, participants will be provided with an accelerometer (wGT3X-BT, ActiGraph LLC) to quantitatively measure activity and sleep. The wGT3X-BT accelerometer measures movement along 3 different axes: x-, y-, and z-axes. It is a valid PA measurement tool across many types and intensities of PA [44] that has been used previously to quantify PA in nurses [11] as well as in health professional students (including student nurses) [45]. Participants will wear the accelerometer on their nondominant hip (either clipped on their clothes or using a provided monitor belt) for 7 consecutive days [46], and on their nondominant wrist (using a wrist attachment) during sleep [47,48]. Participants will be instructed to wear the monitor during all waking and sleep hours, and to only remove the device during a shower or to partake in water-based activities. They will be asked to keep a detailed activity and sleep log, recording information such as when purposeful exercise occurs, sleep quality, and tiredness. Participants will be encouraged to maintain their regular activity levels and sleep habits.

After the 7-day data collection, the participant will return the accelerometer and the activity and sleep log. The accelerometer data will be downloaded using ActiLife software (version 6.13.3, ActiGraph LLC), with data further exported to Excel (version 16.4, Microsoft) to complete analyses. We will require a minimum of 4 days of accelerometer wear (confirmed by activity logs) for a participant's data to be considered valid [49,50]. We will not exclude prolonged bouts of inactivity that is accounted for because students may be attending class or might study for prolonged periods of time in a stationary position. If necessary, we will compare activity logs to the daily accelerometry activity records and exclude days where the accelerometer was not worn for >60 consecutive minutes for unaccounted reasons. The intensity of PA will be determined by counts per minute using the Freedson Adult algorithm [51]. These intensity cut-offs were used by our pilot study [30] and another study that examined daily PA via accelerometry in health professional students [45]. Data from the accelerometer will show the total kcals expended per day and the amount of time engaged in sedentary, light, or moderate/vigorous-intensity activity per day, as well as data on sleep times, sleep latency, and sleep efficiency [47].

#### Nutrition

During the same week as their accelerometry data collection, participants will complete a consecutive 3-day diet log (which includes 2 days of the week and 1 day of the weekend) and record all food intake. A 3-day diet log is commonly used to assess nutritional intake [52,53]. Logs will be analyzed with Nutritionist Pro software (Axxya Systems) for multiple outcomes, including total kcal intake and macro and micronutrient content.

#### Stress and Psychological Health

Levels of stress will be assessed using 3 methods: (1) a biochemical analysis of levels of salivary cortisol; (2) resting measures of heart rate variability (HRV), which can provide information on autonomic balance (sympathetic and parasympathetic tone); and (3) the Depression Anxiety Stress Scale (DASS).

For the biochemical analysis of salivary cortisol, participants will be asked to submit 2 saliva samples. Participants will collect 2 saliva samples (4-5 ml) in provided sample tubes, once during the morning and once during the evening on the first full day of their accelerometry collection week. Participants will record the day and time of their saliva sample collection, and will keep the salivary samples in the freezer until they are able to return their samples to the research laboratory. Samples will be transported back to the lab in a cooler. Cortisol, which is reflective of current stress levels, will be analyzed via ELISA (Eagle Biosciences).

For analysis of HRV, participants will have their heart rate monitored in lab at their study visit (following the collection of metabolic health measures) for 10 minutes in the supine position and 10 minutes in the standing position using a GPS sports watch (Polar V800). This information will be downloaded using Flowsync software (Polar) and analyzed using Kubios HRV software (Kubios Oy), which performs a fast Fourier transformation on the data collected to determine autonomic balance.

Students will complete the DASS at their study visit. The DASS is a widely used tool that has been validated in many populations to assess the emotional states of depression, anxiety, and stress [54]. There are reference values to which DASS scores can be compared [55]. It is important to note that the DASS does not measure clinical outcomes but rather the emotional states of anxiety, stress, and depression. The DASS is not intended to be used as a diagnostic tool for clinical cases. It considers how an individual has felt over the past week and is a 42-question scale that will take approximately 15 minutes to complete.

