High obesity rates and sedentary behavior in RNs are particularly concerning for two reasons. First, a nurse's own behavior may influence their nursing practice. Indeed, RNs who exercise regularly are more likely to promote PA to their patients compared to those who are sedentary [10]. In addition to potentially impacting patient care, obesity and sedentary behavior in RNs are concerning because nurses are not optimizing their own physical and mental health. RNs who are overweight or obese suffer from impaired cardiovascular and metabolic health [11]. As well, the nursing profession is associated with high levels of psychological stress [12,13] and high rates of depression compared to the general population [14,15]. It is widely recognized that PA is important for maintaining both physiological and mental health [16,17]. Physical inactivity may actually worsen mental health in RNs; in one study, physical inactivity was associated with psychological distress, even after adjusting for age, job demands, and job control, among other factors [18]. Sleep also contributes to mental health and overall well-being [19], and RNs report being fatigued and having poor sleep habits [20-22]. Shift work is associated with higher BMI and waist-to-hip ratio (WHR) [23], while participation in PA is associated with improved sleep in non-nurse populations [24-27]. Thus, obesity, poor PA, and reduced sleep are concerning in RNs, considering the negative effect of such lifestyle choices on nurses' physiological and mental health.

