### Statistical Analysis

The demographic characteristics of the participants will be assessed using descriptive statistics. The association between metabolic status (BMI, WHR, body fat percentage, blood pressure, and fasting blood glucose) and PA outcomes, sleep quantity and quality, nutrition, and stress will be examined by linear regression analyses. To examine differences by year of study, 1-way analyses of variance (ANOVAs) will be conducted comparing metabolic health status, PA, sleep, nutrition, and stress. Bonferroni post-hoc testing will be conducted if significant group differences are present. To determine the association between PA, sleep, nutrition, and stress with metabolic health (ie, BMI, WHR, blood pressure, blood glucose), we will conduct linear regression analyses in all nursing students, and by year of study.

To determine the ability of PA, sleep, nutrition, and stress to discriminate prevalent overweight and obesity, participants will be placed into one of 2 groups: overweight or obese versus not overweight or obese, based on the WHO’s BMI and WHR cut-offs [40]. Logistic regression and receiver operating characteristic (ROC) curves will be constructed for each lifestyle variable [expressed as area under the ROC curves (AUROC) with 95% confidence intervals (CI)]. Similar analyses will be conducted using a composite indicator of metabolic status (incorporating obesity status, blood pressure, and fasting blood glucose). Additional analyses adjusted for age, gender, year of nursing study (including exposure to practicum), semester of school, and other potential confounding variables (such as prior physical activity habits) will be conducted as deemed necessary. Statistical analyses will be performed in Stata (version 16.1, StataCorp LLC).

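### Saliva sampling is fixed only as morning and evening, with no window or anchor to waking, so cortisol used as a stress measure will carry timing variation

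*Protocol article*

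**What the plan says.** In the protocol article, Stress and Psychological Health, salivary cortisol is the first of three stress measures, beside resting heart rate variability and the DASS. Participants collect the samples themselves, "once during the morning and once during the evening on the first full day of their accelerometry collection week". On timing the section adds only this: "Participants will record the day and time of their saliva sample collection". On interpretation it says: "Cortisol, which is reflective of current stress levels, will be analyzed via ELISA".

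Physical Activity and Sleep states that the accelerometer is worn on the wrist during sleep and yields activity data "as well as data on sleep times, sleep latency, and sleep efficiency". The accompanying log is described as follows: "They will be asked to keep a detailed activity and sleep log, recording information such as when purposeful exercise occurs, sleep quality, and tiredness". Time of waking is not among the examples given for the log.

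Statistical Analysis enters stress in the linear regressions, in the one-way ANOVAs by year of study, and in the logistic and ROC analyses. The named adjustment variables are age, gender, year of study with practicum exposure, semester and prior activity habits. The list is open-ended and adjustment is discretionary. Saliva collection time and time since waking are not named.

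**The concern.** Asking for both a morning and an evening sample already implies that cortisol depends on the time of day. Yet morning can mean on waking for one student and several hours after waking for another, and both samples comply. The type of day is also open. The first full day of the accelerometry week depends on when the visit took place, so it may be a class day, a practicum day or a free day.

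The first consequence is noise. Timing variation in cortisol weakens any association with BMI, WHR, body fat, blood pressure or glucose, and makes differences by year harder to see. The second is conditional: if time since waking differed systematically between groups of students, part of a cortisol difference would reflect schedule and not stress. This deserves attention because the Significance section says that the factors found to be associated with poor metabolic health will become the targets of a lifestyle intervention.

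**Working it through.** **Text check.** The article fixes measurement conditions for its other measures: a 12-hour fast for glucose; about 5 minutes seated and two readings 60 seconds apart for blood pressure; 10 minutes supine and 10 minutes standing for heart rate variability; two weekdays and one weekend day for the diet log. For saliva it gives volume, storage, transport and assay, but only part of the day for timing. The analysis section does not make up for this, since a one-way ANOVA carries no covariate and sampling time is not a named adjustment variable.

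**Illustration of size.** The article gives no figure to reproduce. All three inputs below are assumptions:
- b, the change in log cortisol per hour since waking: 0.05 to 0.15
- SD_t, the spread between students of sampling time relative to waking: 0.5 to 2 h
- SD_o, the between-student SD of log cortisol from everything other than timing: 0.4 to 0.6

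If timing is unrelated to the outcome:
- timing share of variance = (b × SD_t)² / [(b × SD_t)² + SD_o²]
- factor multiplying a correlation = √(1 − share)

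| b | SD_t (h) | SD_o | Share | Factor |
|---|---|---|---|---|
| 0.05 | 0.5 | 0.6 | 0.002 | 0.999 |
| 0.05 | 1 | 0.4 | 0.015 | 0.992 |
| 0.10 | 1 | 0.6 | 0.027 | 0.986 |
| 0.10 | 1 | 0.4 | 0.059 | 0.970 |
| 0.15 | 1 | 0.4 | 0.123 | 0.936 |
| 0.10 | 2 | 0.4 | 0.200 | 0.894 |
| 0.15 | 2 | 0.4 | 0.360 | 0.800 |

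Worked extremes:
- Smallest: (0.05 × 0.5)² = 0.000625, and 0.000625 / (0.000625 + 0.36) = 0.002; √0.998 = 0.999.
- Largest: (0.15 × 2)² = 0.09, and 0.09 / (0.09 + 0.16) = 0.36; √0.64 = 0.80.

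The slope of a single-predictor regression on log cortisol shrinks by 1 − share, that is by a factor of 0.998 to 0.64 at the same extremes.

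The calculation treats one sample with a constant hourly slope. No separate calculation was made for the evening sample.

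**Bias.** If two groups differ by d hours in mean time since waking, log cortisol differs by b × d for reasons other than stress. The article gives no value for d, and with d = 0 there is no bias.

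**The case against.** The strongest reply is that this is a condensed article. An instruction sheet for participants may set sampling times, and the choice of covariates may sit in an analysis plan that is not shown. That is fair for the covariates, and the adjustment list is open-ended. It is less persuasive for collection: the article does state when samples are taken, in a section detailed enough to give volume and transport, and what it states is loose.

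The second reply is that much can be recovered. Sample time is recorded, and the device is handed out at the visit and worn during sleep, so the night before the saliva day should be captured and time since waking derived. This largely stands, and it makes the problem partly repairable in analysis. It is not assured: accelerometer data count as valid with 4 days of wear, so the saliva day may lack usable data, and wake time is not a stated log entry.

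A reader might go further and infer that practicum students rise early or work nights, so that a cortisol difference by year would be an artefact. With a fall of 5% to 15% per hour and a gap of 2 to 3 h, that would give a difference of 1 − 0.95² = 10% to 1 − 0.85³ = 39%. The documents do not support this. They never say that these students work nights or start early. The shift-work statement in Background and Rationale belongs to the discussion of registered nurses, and the demographic questionnaire only asks whether students work or volunteer. The gap has no source. Nor can the spread be taken from clock times: a uniform spread over 06:00 to 12:00 has an SD of 6/√12 = 1.73 h, but late risers may also sample later, so the spread in time since waking can be smaller.

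**Conclusion.** The point holds as a weakness of measurement that should be corrected before data collection. As written, the plan lets time since waking vary freely, reads the result as stress, and assigns the recorded time no use. Under the assumed inputs the loss ranges from negligible (factor about 1.00, if students happen to sample at similar times after waking) to material (0.80, if timing varies by about 2 h and the slope is steep). The article does nothing to secure the favourable end.

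Confounding by year or practicum is a possibility that depends on schedules the article does not describe; it is not a demonstrated bias. Nor does the whole stress domain fall with cortisol, since heart rate variability and the DASS do not depend on saliva timing.

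**What to change.** In Stress and Psychological Health, have the morning sample taken at one fixed interval after the participant's own waking, the same for everyone, and the evening sample at bedtime. Ask participants to write wake time and type of day (practicum, work or free) beside the sample time, and check wake time against the accelerometer sleep data.

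In Statistical Analysis, use log cortisol adjusted for time since waking in the regressions, and replace the unadjusted one-way comparison of cortisol by year with one that carries the same covariate. Add a sensitivity analysis that excludes samples outside the fixed window.

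The cost is a line in the participant instructions, one extra log entry, and a few samples set aside in the sensitivity analysis. No further samples or visits are needed. The article reports that the ethics application was still being completed and that data collection had not begun, so the change can be made before the first sample is taken.

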### Statistical Analysis

The demographic characteristics of the participants will be assessed using descriptive statistics. The association between metabolic status (BMI, WHR, body fat percentage, blood pressure, and fasting blood glucose) and PA outcomes, sleep quantity and quality, nutrition, and stress will be examined by linear regression analyses. To examine differences by year of study, 1-way analyses of variance (ANOVAs) will be conducted comparing metabolic health status, PA, sleep, nutrition, and stress. Bonferroni post-hoc testing will be conducted if significant group differences are present. To determine the association between PA, sleep, nutrition, and stress with metabolic health (ie, BMI, WHR, blood pressure, blood glucose), we will conduct linear regression analyses in all nursing students, and by year of study.

To determine the ability of PA, sleep, nutrition, and stress to discriminate prevalent overweight and obesity, participants will be placed into one of 2 groups: overweight or obese versus not overweight or obese, based on the WHO’s BMI and WHR cut-offs [40]. Logistic regression and receiver operating characteristic (ROC) curves will be constructed for each lifestyle variable [expressed as area under the ROC curves (AUROC) with 95% confidence intervals (CI)]. Similar analyses will be conducted using a composite indicator of metabolic status (incorporating obesity status, blood pressure, and fasting blood glucose). Additional analyses adjusted for age, gender, year of nursing study (including exposure to practicum), semester of school, and other potential confounding variables (such as prior physical activity habits) will be conducted as deemed necessary. Statistical analyses will be performed in Stata (version 16.1, StataCorp LLC).

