### Significance

The current study will be the first published research to examine the relationship between lifestyle choices and metabolic status in nursing students attending a Canadian institution. More importantly, the results of this study will be used to inform a lifestyle intervention for nursing students. To our knowledge, there are only 2 published PA and lifestyle intervention studies that target nursing students. In one study, nursing students and student midwives (N=182) from the UK were randomized into a control or an intervention group. Students in the intervention group received an education package and created a nutrition and physical activity plan. Following the 4-month intervention, the BMI of the overweight participants decreased, indicating that education and accountability may influence exercise participation in nursing and midwifery students [35]. In a second study, a convenience sample of 30 nursing students from a university in the United States who wanted to increase their PA levels were invited to participate in an exercise intervention. Students were asked to exercise for 30 minutes at least 3 times per week. Following one university semester of the intervention, students had reduced body fat percentages and BMIs, and higher levels of self-reported PA [36]. These studies support the idea that a lifestyle intervention can positively affect metabolic health status in nursing students.

The results of this study will directly inform a lifestyle intervention for nursing students that targets the improvement of their health and well-being, specifically addressing the most prominent factors associated with their poor metabolic health status. For example, if reduced PA, poor nutrition, and lack of sleep are all associated with worse metabolic health in nursing students, the developed intervention will focus on improving these outcomes. The development of an intervention will target the improvement of both the physical and mental health of nursing students. This intervention has the potential to influence future nursing practice since research highlights that RNs who are physically active will be more likely to counsel their patients to be physically active [10].

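### Discrimination is planned one lifestyle variable at a time, which cannot show what each factor adds beyond the others or how well the four domains discriminate together

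*Protocol article*

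**What the plan says.** The Statistical Analysis section of the protocol article splits participants into overweight or obese versus not, using WHO cut-offs for BMI and WHR. It then states: "Logistic regression and receiver operating characteristic (ROC) curves will be constructed for each lifestyle variable", each curve summarised by an AUROC with a 95% confidence interval. For the second binary outcome it adds: "Similar analyses will be conducted using a composite indicator of metabolic status".

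Adjustment is described as "Additional analyses adjusted for age, gender, year of nursing study (including exposure to practicum), semester of school, and other potential confounding variables", with the qualifier "such as prior physical activity habits) will be conducted as deemed necessary". No concurrent lifestyle factor is named there as a covariate.

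Several predictors are considered together in one place only: the sample-size text (Overview of Study Design, Timeline, and Participant Selection). It sizes a linear regression for 4 predictors and then for 7, covering four activity intensities, nutrition, sleep and stress.

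On use of the results, Purpose and Objectives sets out to characterise the factors that discriminate metabolic health. Significance says that the later intervention will be built by "specifically addressing the most prominent factors associated with their poor metabolic health status". The Discussion says the study will determine which factors an intervention should target.

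**The concern.** The article itself reports that the lifestyle factors are linked. Background and Rationale notes that "participation in PA is associated with improved sleep in non-nurse populations" and that in one study of nurses "physical inactivity was associated with psychological distress". When predictors are correlated, a single-variable AUROC mixes a factor's own contribution with what it shares with the others. Choosing among factors, or calling some more prominent, calls for a view of what each adds given the rest.

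Two things are at stake. A factor with no contribution of its own could be read as a discriminator in its own right and put forward as an intervention target. And the study would not report how well the four domains together identify students with overweight/obesity or poor metabolic status.

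**Working it through.** The plan gives no figure for the discrimination analysis. Its sample sizes of 87 and 103 belong to the linear regression and do not bear on this point. The size of the problem therefore has to be illustrated under assumptions.

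**Inputs from the article.** Planned N = 320, 80 per year of study. Pilot BMI by year group: 20.3 ± 2.3, 23.7 ± 1.9 and 25.4 ± 2.5 kg/m² (first, second, third/fourth year).

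**Assumed inputs (not in the article).** The ± values are SDs of normal distributions. The overweight cut-off is 25. Factor A discriminates with AUROC 0.65. Factor B contributes nothing given A but correlates with it at r = 0.3 or 0.5.

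**Step 1: prevalence.** Upper-tail areas at 25:
- First year: (25 − 20.3)/2.3 = 2.04, giving 2%.
- Second year: (25 − 23.7)/1.9 = 0.68, giving 25%.
- Third/fourth year: (25 − 25.4)/2.5 = −0.16, giving 56%.

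Weighted 80:80:160, this is 0.25 × 2% + 0.25 × 25% + 0.50 × 56% ≈ 35%, or about 112 cases and 208 non-cases.

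**Step 2: B's marginal AUROC.** In the binormal model AUROC = Φ(d/√2). For A, d = √2 × Φ⁻¹(0.65) = 0.545. B's mean shift is r × d:
- r = 0.3: 0.163/√2 = 0.116, so AUROC = 0.546.
- r = 0.5: 0.272/√2 = 0.193, so AUROC = 0.576.

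With shifts (d, rd) and correlation r, the joint logistic coefficient of B is exactly zero, so B has no contribution of its own.

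**Step 3: how often B's interval excludes 0.5.** The Hanley-McNeil SE with 112 cases and 208 non-cases is about 0.034.
- r = 0.3: 0.046/0.034 = 1.35; Φ(1.35 − 1.96) ≈ 27%.
- r = 0.5: 0.076/0.034 = 2.24; Φ(2.24 − 1.96) ≈ 61%.

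Simulation (1,500 runs) agrees:

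| r | B's AUROC | B flagged alone | B flagged in joint model |
|---|---|---|---|
| 0.3 | 0.546 | 28% | 5.4% |
| 0.5 | 0.576 | 61% | 4.9% |

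**Step 4: sensitivity to the assumptions.** A second simulation (N = 320, 1,000 runs per setting) used prevalence 25% or 40% and an odds ratio per SD of 1.5 or 2.0 for the true discriminator. The factor without its own effect was flagged by its single-variable interval as follows:

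| Correlation | Flagged alone |
|---|---|
| 0 | about 5% |
| 0.2 | 10–18% |
| 0.3 | 15–34% |
| 0.5 | 32–79% |

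In the joint model it was flagged in about 3–7% of runs throughout.

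**Step 5: joint discrimination.** Take four factors, each with AUROC 0.60, so d = √2 × Φ⁻¹(0.60) = 0.358. With common correlation r, D² = 4d²/(1 + 3r) and joint AUROC = Φ(D/√2):

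| r | 0 | 0.2 | 0.3 | 0.5 |
|---|---|---|---|---|
| Joint AUROC | 0.694 | 0.656 | 0.643 | 0.626 |

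The same four single-variable curves are compatible with any of these values, so they cannot tell the reader which one applies.

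**The case against.** The strongest reply is that a single-variable AUROC answers the question the section poses, namely the ability of each factor to discriminate. **This stands.** In the illustration B truly has AUROC 0.546 or 0.576, so it does discriminate marginally. A reader might take the 28% and 61% as false-positive rates of the ROC analysis. They are not: they are the power to detect a real marginal AUROC. They become misleading only if that result is read as an independent contribution.

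Second, the targets are described in terms of association, and the linear regression sized for up to 7 predictors is the primary tool for that. **This stands in part.** That regression, apparently planned with the predictors together, helps separate correlated factors for the continuous outcomes. It gives no AUROC and does not cover the overweight/obesity grouping or the composite.

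Third, the adjustment clause is open-ended, the article is condensed, and no analysis plan is shown. A reader might infer that joint discrimination will never be estimated, or that mutual adjustment is excluded. The article does not say so: its wording would permit such a model. But adjustment is optional and names no concurrent lifestyle factor, whereas the per-variable unit is stated outright.

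Fourth, mutual adjustment can mislead too. Background and Rationale suggests that PA may act on sleep and mental health. If sleep mediates PA, a joint model could make PA look unimportant. **This stands**, and it rules out choosing targets from adjusted results alone.

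Finally, the Discussion concedes that the study shows correlation and not causation. That is a fair caveat, but the same paragraph still relies on the results to learn which factors to target.

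**Conclusion.** The point holds as a gap between the stated analysis and its intended use. The single-variable curves are valid, but as marginal description only. Without a joint model for the binary outcomes, the study cannot say what each domain adds beyond the others or how well the four discriminate together.

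A factor with no contribution of its own can, not will, appear as a discriminator. The size is roughly 28% to 61% of studies when the factor is read alone, against about 5% in a joint model, given a true discriminator with AUROC 0.65, correlation 0.3 to 0.5, N = 320 and 35% prevalence. Across the wider assumptions tried (correlation 0.2 to 0.5) the range is about 10% to 79%, against 3% to 7%. The article supplies no correlations or effect sizes and no prevalence for the composite, so these figures illustrate the problem and do not predict its size.

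**What to change.** In Statistical Analysis, label the single-variable ROC curves as marginal, descriptive results. For each binary outcome (overweight/obesity and the composite) add one logistic model with one pre-named measure each for PA, sleep, nutrition and stress. Report:
- mutually adjusted odds ratios with confidence intervals;
- the joint AUROC, corrected for optimism (for example by bootstrap);
- the change in AUROC when each domain is removed.

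Limit any claim of independent discrimination to this model. When choosing targets, set marginal and adjusted results side by side and state that sleep or stress may mediate PA, so that a factor is not dropped merely because it acts through another.

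The cost is a few lines of Stata and one table, with no new data. At the assumed 35% prevalence, about 112 cases for four predictors is 28 per predictor. The downsides are that one measure per domain must be chosen in advance and that intervals for correlated domains will be somewhat wider.
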